### Blinding

Treatment allocation to ultrasound and sham-ultrasound is blinded to the subject. Blinding of the investigator is not possible as sham-ultrasound is applied according to the normal routine without turning on the power.

Day and Altman suggest blinding assessment by using non-involved assessors to record outcome variables [43]. However this is not feasible in the context of the given study. To allow readers to judge possible information bias, assessment routine and blinding are stated explicitly [44]. Blinding is impossible as treatment exposure can be discovered by interviewing the study participants (except the differentiation between US and SUS, which is kept single-blinded until the end of the study). Furthermore, independent assessors are not available, as quantification of outcomes needs specific know-how and man-power of our institution is limited. Moreover, instrumented gait analysis and assessment of postural control using pressure mats are relatively objective measures with limited possibility of exerting external influence. Strength measures may be more susceptible to external influences, as motivation is an important factor for maximum strength development. To minimize potential influence of the assessors, instructions are standardized and always given by the same investigator. SF36 and WOMAC are self-administered psychometric instruments. Subjects are introduced to the questionnaires at the beginning of the baseline assessment before treatment allocation is done. Subjects may contact the study nurse in case of questions. However, there is no assessor recording the responses of the subjects to the questionnaires and therefore no need for blinding.

### Participants

217 men and women aged between 18 and 85 years are recruited via regional press, flyers in medical and physiotherapeutic practices, the outpatient clinic of the Department of Sports Medicine, and personal communication. Eligibility is confirmed by verbal and clinical examination carried out by the principal investigator of the study (medical doctor). Criteria for hip osteoarthritis are defined according to the clinical criteria of the American College of Rheumatology [45]. Other inclusion criteria are: (i) health-related eligibility in terms of physical and mental ability to participate in the interventional program; (ii) sufficient time to keep therapeutic appointments; (iii) capacity to consent. Annotation: Subjects can also be included in the case of a contra-lateral hip replacement, as long as one side has a hip osteoarthritis according to the above mentioned criteria.

Exclusion criteria are: (i) instable anchoring of an artificial hip replacement; (ii) luxation as an adverse event of artificial hip replacement; (iii) predominant knee OA; (iv) pathologies in the region of the lower extremities or lower back that are not related to OA and need medical treatment; (v) inability to ambulate without walking aids; (vi) hip joint injections within the last 3 months; (vii) surgery at the lower extremity within the last 3 months; (viii) previous trauma at the hip or pelvis with subsequent development of a secondary arthrosis; (vix) known endocrinological cause of hip OA (hyperuricaemia, hyperparathyroidism, hyperuricaemia); (x) verified metabolic cause of hip OA (haemochromatosis, rachitis, chondrocalcinosis, ochronosis); (xi) state after aseptic osteonecrosis (Perthes' disease); (xii) neurological disease leading to sensomotoric deficits; (xiii) cardio-vascular disease or other co-morbidities resulting in a profoundly decreased physical capacity in everyday life and that are known as contraindications for physical activities (i.e. cardiac insufficiency NYHA III-IV, terminal renal insufficiency); (xiv) medical exercise therapy or physiotherapy using weight machines and comparable resources during the last 3 months and carried out at least 6 times; (xv) specific group or individual intervention to address hip OA in the last 3 months (minimum 1x/week, 30 minutes or more); (xvi) physical therapy to address hip OA (minimum 1x/week); (xvii) novel initiated physical exercise within the last 3 months (minimum 1x/week to be short of breath for at least 30 minutes); (xviii) abuse of drugs or alcohol; (xix) participation in another clinical trial in the last four weeks; (xx) no compliance; (xxi) acute illness.

Ethical approval has been obtained from the Ethics Committee of the University of Tuebingen (358/2010BO2). All participants will provide written informed consent.

### Interventions

All participants are requested to refrain from seeking other forms of treatment during the 12 week-intervention period from M1 to M2. Subsequently, subjects are offered to participate in the intervention group they were not allocated to before for another 12 weeks.

Many studies compare exercise interventions with an untreated control group (parallel group design or waiting list design) [26,46]. However it is well known that a placebo is significantly superior to the effect of untreated controls [47]. The used study design will help to distinguish between treatment effects of physical exercise, attention control (sham ultrasound), and unaccompanied study participation (no intervention group).

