### Study purpose

The primary aim of this study is to determine whether a 12-week intervention program comprising group and home-based exercises decreases bodily pain in subjects with hip osteoarthritis in comparison to a non-treated control group. Efficacy is quantified by the subscale *bodily pain *of the SF36. The secondary aim is to determine whether this exercise regime can improve function, health-related quality of life, strength of hip surrounding muscles, postural control in bi-pedaled, tandem-, and single leg stance, joint function, and gait parameters in comparison to a non-treated control group, an attention control group (sham ultrasound), and an ultrasound group. Ultrasound therapy is only investigated in an explorative manner. Follow-up data are recorded to evaluate the sustainability of the interventional programs over another 40 weeks.

It is hypothesized that a 12-week intervention program will (1) decrease pain, and (2) improve physical function in comparison to a non-treated control. It is further hypothesized that (3) the efficacy of the exercise regime is superior to the efficacy of an intervention solely aiming for attention control, and (4) that effects are long-acting.

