#### No intervention group (CO)

Subjects allocated to this group do not receive any therapeutic intervention between M1 and M2. They are requested to continue their usual routine.

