### Outcome measures (Figure 1)

Participants are assessed at baseline (M1), and 12 weeks after the intervention period (M2). Patient characteristics (age, gender, height, weight) are evaluated at the baseline assessment. Questionnaires (WOMAC, SF36), measures of postural control, clinical gait analysis, functional tests (passive range of motion (ROM), muscle flexibility), and isometric strength measures are evaluated at M1 and M2. Previous physiotherapy and/or exercises, medication, and pain (retrospective time frame of four weeks) are evaluated at M1 and noted each subsequent month up to M2 in a logbook. Satisfaction with the therapy regime is assessed with a questionnaire at M2 and M3. 16 weeks past M2 (M3) and 24 weeks past M3 (M4), participants are contacted again via telephone to assess WOMAC, SF36, previous physiotherapy and/or exercises, and medication.

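### The offer of another intervention after M2 means that M3/M4 differences between arms are not a clean test of whether Hip School effects last (hypothesis 4)

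*Protocol article*

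**What the plan says.** The Study purpose section lists four hypotheses, the last being "and (4) that effects are long-acting". It gives the reason for follow-up as: "Follow-up data are recorded to evaluate the sustainability of the interventional programs over another 40 weeks".

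The Outcome measures section sets the times: "16 weeks past M2 (M3) and 24 weeks past M3 (M4), participants are contacted again via telephone to assess WOMAC, SF36". M3 is therefore M2 + 16 weeks, and M4 is M2 + 16 + 24 = 40 weeks.

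The Interventions section protects only the first 12 weeks: "All participants are requested to refrain from seeking other forms of treatment during the 12 week-intervention period from M1 to M2". The next sentence makes the offer: "Subsequently, subjects are offered to participate in the intervention group they were not allocated to before for another 12 weeks". It excepts no group, and it does not state a start date or which intervention each arm is offered. The description of the control arm has the same time limit: "Subjects allocated to this group do not receive any therapeutic intervention between M1 and M2".

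The Statistical analysis section names an intention-to-treat analysis of all randomised participants, group and time as factors for continuous outcomes, and last score carried forward for missing data. It gives no rule for treatment taken up after M2.

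**The concern.** Both measurements that bear on durability fall after the offer. From M2 on, CO and sham participants may have had Hip School, and Hip School (HS) participants may have had something else. A shrinking HS–CO difference at M3 or M4 then has two explanations that the data cannot separate: the HS effect faded, or the comparators caught up. A null contrast at 40 weeks could be reported as loss of effect when the effect had in fact lasted. Durability is one of the four numbered hypotheses and the stated reason for the follow-up.

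**Working it through.** **Timing.** If the second 12-week course starts directly after M2 (an assumption, since no start date is given), it ends 16 − 12 = 4 weeks before M3 and 40 − 12 = 28 weeks before M4. At M3 a CO participant who took Hip School would be about 4 weeks past it, and an HS participant 16 weeks past it.

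**The plan's own figure.** The sample size section gives 60 per group, 80% power, and a two-group t-test at two-sided 0.05. It prints neither the minimum clinically important difference nor the SD, so 60 cannot be reproduced forward. Solving the noncentral-t power equation backwards for n = 60 gives a standardised effect of d = 0.516, and entering that value returns n = 60. The plan states no power for M3 or M4.

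**Expected contrast after M2.** Let r be the share of the M2 effect that HS retains and p the share of CO that takes up Hip School. Assume that those who cross over gain the full M2 effect, that the rest of CO gains nothing, and that HS gains nothing from its own second course. Then

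HS − CO at M3 = r·d − p·d = (r − p)·d.

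The documents give neither r nor p.

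**Full retention (r = 1), 60 per arm, two-sided 0.05:**

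| CO uptake p | Contrast (1 − p) × 0.516 | Power |
|---|---|---|
| 0% | 0.516 | 80% |
| 10% | 0.464 | 71% |
| 25% | 0.387 | 56% |
| 50% | 0.258 | 29% |
| 80% | 0.103 | 9% |
| 100% | 0 | 5% (the significance level) |

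**Ambiguity.** Full retention with half of CO crossing over gives 1 − 0.5 = 0.5 of the M2 effect. Half retention with no uptake gives 0.5 − 0 = 0.5 as well. The contrast alone cannot tell these apart.

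**Sign.** The contrast is negative only when r is below p. With r = 0.6 and p = 0.8 it is −0.2 of the M2 effect. With r = 1 it is never negative, because p cannot exceed 1.

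**Missing-data rule.** Suppose values after a second intervention were set to missing and the printed rule then applied. The M2 score would be carried to M3 and M4, and the M2-to-M3 change for those participants would be zero by construction. That would manufacture durability.

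**The case against.** The strongest reply is that the criticised analysis is partly inferred. The Statistical analysis section does not say that group × time extends to M3 and M4. Hypothesis 4 names no comparator, whereas the other three do. It can be read as maintenance within the HS arm, and follow-up modelling is something an article commonly leaves to a fuller plan. This stands as far as it goes: the text does not commit to a randomised comparison at M3/M4. It does not rescue the hypothesis, because the HS arm gets the same offer and its course after M2 has no unexposed control.

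A second reply is that the offer is voluntary and uptake is unstated. This also stands. A reader might infer that M3/M4 cannot show durability at all, but that needs material uptake. At 10% the contrast is diluted (about 71% power), not void.

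A third reply is that other physiotherapy and exercise are already asked about at M3 and M4. That helps describe uptake, but comparing participants by what they actually took is no longer a randomised comparison. If the logbook's four-week recall also applies to these calls, a course that ended about 4 weeks before M3 could be missed.

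Two further inferences are tempting and unsupported. One is that a fully lasting effect would look reversed; the formula above rules this out. The other is that the offer breaks the ultrasound/sham blinding, "which is kept single-blinded until the end of the study". The text does not say that these participants are offered the other ultrasound arm, and they could be offered Hip School without learning which setting they had.

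**Conclusion.** The concern holds in a limited form. The plan offers a further intervention to participants of every arm before both measurements on which its durability hypothesis rests, and prints no rule for handling uptake. With material uptake, M3/M4 differences between arms measure earlier against optional later access, and a lasting effect is pulled towards zero.

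The size depends on uptake, which the documents do not give. Power is about 71% at 10% uptake and 9% at 80%, given full retention, equal benefit in those who cross over, no gain to HS from its own second course, d = 0.516 and 60 per arm. These figures are illustrative and contradict no figure in the plan.

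The primary endpoint and every other M1–M2 comparison precede the offer and are untouched. The point should be fixed, but it does not threaten the trial's main result.

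**What to change.** 1. Reconcile the Interventions section with hypothesis 4 and the sustainability aim, stating which arms are offered what after M2 and when.
2. Confine confirmatory randomised group × time inference to M1–M2.
3. Label M3/M4 differences between arms as immediate versus optional deferred access, and make hypothesis 4 descriptive.
4. In the existing M3 and M4 calls, record the type and start date of any second intervention since M2. Report uptake by arm.
5. Report the within-HS change from M2 to M3 and M4 with confidence intervals, described as uncontrolled.
6. State that last score carried forward is not applied to values after a second intervention. Use a stated missing-data assumption with a sensitivity analysis instead.

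The cost is revised wording and a short addition to two planned calls, with no new visit or outcome. The downside is a weaker long-term claim.

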#### Hip School(HS)

The Hip School program is a comprehensive, pre-defined 12-week training program. Not all exercises can be displayed in detail as this would be beyond the scope of this study protocol. However, some details are listed below to allow an opinion to be made on relevant issues of the training program.

The Hip School comprises group (1x/week, 60-90') and home based exercises (2x/week, 30-40'). Group size is restricted to a maximum of 15 participants. Elastic rubber bands, stability trainers (pads), exercise balls and exercise mats are used as training devices. Group and home training sessions include hip specific elements of motor learning and mobilization, strength training and exercises to improve postural control, as specified below. Group sessions further include education related to exercises, such as information on anatomical basics and training modalities. The sessions enhance social contacts by having group-based introductions and feedbacks before and after the exercises, and by enforcing partner and group exercises. In the group lessons, subjects are introduced to the exercises they have to do at home. In addition, subjects receive exercise leaflets with pictures of the exercises and written instructions every week.

Detailed description of group and home-based training modalities:

Mobility exercises include elements to increase flexibility of the lumbar spine, pelvis and hip joints. An example for sagittal plane motion is given in Figure 2. Muscle stretching mainly addresses hip and knee flexors and extensors and hip adductors. Perception skills are trained to allow proper exercise execution, and to enhance motor control.

**Figure 2 F2:**
[figure not shown]
**Mobilisation exercise**. Example of an exercise for lumbar spine, pelvis and hip joint mobilisation.

Strength training comprises open and closed kinematic chain exercises for extensors, flexors, abductors and adductors of the hip, as well as flexors and extensors of the knee. Examples for open and closed kinematic chain exercises for hip extensors are given in Figures 3 and 4. Intensity and structure of the exercises follow a progressive concept (Table 1) and are monitored using a Borg Scale.

**Figure 3 F3:**
[figure not shown]
**Strength training for hip and knee extensors**. Example of an exercise for closed kinematic chain training.

**Figure 4 F4:**
[figure not shown]
**Strength training for hip extensors**. Example of an exercise for open kinematic chain training.

**Table 1 T1:** Training progression for strength exercises.

Week	Objective	Intensity (% max strength)	Repetitions/Sets
**1-3**	Motor learning	< 30%	≥ 30/1

**4-8**	Strength endurance	30-40%	20-25/2-3

**9-12**	Endurance & maximum strength	40-70%	10-15/3-4

Leg-alignment training is included in all exercises for postural control. These exercises also follow a progressive training concept, as displayed in Figure 5 for static conditions. Week 9-12 includes further dynamic exercises.

**Figure 5 F5:**
[figure not shown]
**Progressive training concept**. Procedural method for static exercises of postural control.

#### No intervention group (CO)

Subjects allocated to this group do not receive any therapeutic intervention between M1 and M2. They are requested to continue their usual routine.

#### Sham ultrasound (SUS)

Frequency, duration, and total number of treatments for sham ultrasound are equivalent to the procedure described for ultrasound. However, intensity is turned off.

#### Ultrasound (US)

Despite low quality of given evidence, therapeutic ultrasound may be beneficial for patients with osteoarthritis of the knee [48]. In subjects with hip OA, ultrasound in addition to standard physiotherapy has been shown to be superior in terms of a longitudinal positive effect on pain, functional status, and physical quality of life in comparison to a standard physiotherapy with and without sham ultrasound [49]. Safety of this intervention has yet not been disproved, and to date no serious adverse events have been reported [48]. In the context of this study, ultrasound is used as a comparable verum intervention to sham ultrasound (SUS). It would be unethical to include SUS only, as subjects are told that they may receive real ultrasound or sham ultrasound. US will be applied in a minor number of subjects, serving to explore its potential benefits in the treatment of hip OA in a different dosage as investigated before [49]. Ultrasound is applied with a commercially available ultrasound apparatus (Zimmer MedizinSysteme GmbH, Germany). Instrument adjustments and treatment modalities are presented in Table 2.

**Table 2 T2:** Instrument adjustments and treatment modalities for ultrasound therapy.

Parameter	Setup
**Frequency**	1 MHz
**Mode**	Continuous mode
**Intensity**	1 W/cm^2^
**Head size**	5 cm^2^
**Duration of treatment**	15' (5' each from anterior, lateral, and posterior)
**Treatment area**	70-80 cm^2 ^about the affected hip joint
**Treatment frequency**	1/week
**Total number of treatments**	12

### Outcome measures (Figure 1)

Participants are assessed at baseline (M1), and 12 weeks after the intervention period (M2). Patient characteristics (age, gender, height, weight) are evaluated at the baseline assessment. Questionnaires (WOMAC, SF36), measures of postural control, clinical gait analysis, functional tests (passive range of motion (ROM), muscle flexibility), and isometric strength measures are evaluated at M1 and M2. Previous physiotherapy and/or exercises, medication, and pain (retrospective time frame of four weeks) are evaluated at M1 and noted each subsequent month up to M2 in a logbook. Satisfaction with the therapy regime is assessed with a questionnaire at M2 and M3. 16 weeks past M2 (M3) and 24 weeks past M3 (M4), participants are contacted again via telephone to assess WOMAC, SF36, previous physiotherapy and/or exercises, and medication.

#### Questionnaires

The 36-item Short Form (SF36) is a well-established generic health status measure and allows the effect of an OA intervention to be gauged in comparison with other interventions [50]. It comprises different scales, four of them related to physical health (physical functioning, role-physical, bodily pain, general health), and four of them related to mental health (vitality, social functioning, role-emotional, mental health). The primary outcome measure of this study is the subscale bodily pain of the SF36. The other scales and sum scores will also be analysed as secondary outcomes.

The Western Ontario McMasters Universities Osteoarthritis Index (WOMAC^® ^NRS German for Germany 3.1 Index) is a disease-specific instrument used to evaluate self-reported pain, stiffness and functional impairment. It is a valid, reliable and responsive score, easy to complete, simple to score and available in multiple language forms and scaling formats [51].

A five point Likert Scale is used on M2 and M3 to quantify satisfaction with the therapy regime, and whether participants would recommend this therapy to others.

Level of education of the subjects is recorded to control for a recruiting bias.

#### Monthly logbooks

Participants are asked to fill out a monthly logbook between M1 and M2. They have to specify previous physiotherapy and/or exercise, medication, and pain (retrospective time frame of four weeks). This information is also requested on M3 and M4 in the context of the telephone call.

#### Measures of postural control

Postural control is quantified in bi-pedaled, tandem-, and single leg stance on a measuring system for force distribution (FDM System, zebris Medical GmbH, Isny, Germany). The outcome measure for postural control is the total path of the centre of force over the entire trial. Subjects are allowed to familiarize themselves with each mode prior to recording. Modalities of the different tests for postural control are summarized in Table 3. Trials of each mode are averaged prior to further analysis.

**Table 3 T3:** Test modalities for postural control

Test	Position	Recording time	Number of trials
**Bi-pedaled with eyes open**	Feet in parallel position Weight is equally distributed on the feet Knees slightly bended Arms akimbo	10 s each	3 each
**Bi-pedaled with eyes closed**			

**Tandem stance right foot in front**	Feet are placed on a line, one before the other Toes of the rear foot are in contact with the heel of the leading foot Weight is equally distributed on both feet Knees are slightly bended Arms akimbo	6 s each	3 each
**Tandem stance left foot in front**			

**Single-led stance right**	Single led stance Knee of the supporting leg is slightly bended Non-supporting leg is not allowed to touch supporting leg Arms akimbo	6 s each	5 each
**Single-led stance left**			

#### Clinical gait analysis

Participants undergo three-dimensional gait analysis in barefoot and shod conditions at self-selected normal speed that is monitored by light-barriers. After two static trials, participants continuously walk back and forth on an eleven meter walk-way until at least seven valid trials for each side and condition are captured. For the barefoot condition, the walk-way is covered with an EVA-foam (shore 80) to allow a comfortable and natural walking pattern. Kinematic and spatial-temporal data are collected using a Vicon motion analysis system with six cameras (ViconPeak, MCAM M1, 120 Hz, Oxford, UK). Data are analysed with the lower body model of the conventional gait model Plug-in-Gait (Vicon Polygon, Oxford Metrics Ltd., Oxford, UK). Markers are placed on the superior and posterior iliac spines, lateral thigh, and lateral epicondyle of the knee, lateral shank, lateral malleolus, calcaneus, and second metatarsal head. Additional markers are placed on the toe or toe cap, respectively, to ease the detection of toe off.

Outcome measures include the following spatial-temporal variables: stride length, step length, step width, walking velocity, cadence, single and double support time. Other variables of interest include time histories, maximum and minimum joint angles, and ranges of motion of the sagittal plane for pelvis, hip, knee, and ankle joint, as well as pelvic drop and hip adduction and abduction in the frontal plane. Outcome measures of five trials for each limb and condition (barefoot and shod) are extracted and averaged with a customized Matlab routine (Mathworks Inc., Natick, Massachusetts, USA).

